### Statistical analysis plan

Analysis will be performed on the basis of initial treatment allocation; that is the intention-to- treat (ITT) principle.

### Checking for normality and descriptive analysis

Histograms will be graphed to check the distribution of all the continuous variables in the dataset. For descriptive analysis, mean with standard deviation will be reported for symmetrically distributed continuous variables while median with interquartile range will be reported for not symmetrically distributed continuous variables. For categorical data, frequency with percentages will be reported.

### Univariate analysis

Scale examination of all the continuous variables will be carried out. Some of the continuous variables will be transformed into categories where needed. We might need to collapse categories for categorical variables if we have a sparse data problem. Multiple Linear Regression (MLR) will be applied at the univariate analysis level. Each variable will be regressed independently with the primary end-point. Their assumptions will be checked and their significance will be reported. At univariate analysis level, a variable will be considered to be biologically significant as well as statistically significant if the *p* value is less than or equal to 0.10. Crude beta-coefficient with 95 % confidence interval will also be reported.

### Multivariable analysis

A variable having a *p* value of less than or equal to 0.05 will be considered to be clinically significant as well as statistically significant at the multivariable analysis level. All variables that are considered to be significant at the univariate analysis level will need to run through a stepwise model building approach (manual) to obtain a parsimonious model. Multiple linear regression (MLR) will be used to predict the final model. Adjusted beta-coefficients with their appropriate 95 % confidence interval will be reported for the final model. The final model will be assessed for interaction between biologically plausible variables as well as for confounding after checking for interaction; beta-change (15 %) will be considered significant for confounding to be reported. Assessment of multicollinearity between two independent variables will be carried out using appropriate statistical tests. A correlation coefficient of more than 0.80 will be treated as significant for multicollinearity. The model will be assessed for the presence of outliers and influential observations and robust standard errors will be reported if influential observations are found.

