### Sample size calculation

The study is designed to enroll 300 participant dyads (150 participants and 150 caregivers in each group – intervention versus standard care) after inflating 10 % to incorporate attrition and non-compliance. The sample size was calculated keeping in mind the two primary end-points of medication adherence and risk factor control; the primary end-point that gave the highest sample size was kept as the final sample size. This number of participants would provide the study with the ability to detect a 15 % difference among groups with a power of at least 95 %. The proportion of participants achieving control of three modifiable risk factors (blood pressure, blood cholesterol and blood sugar) was assumed to be 0.50 in the treatment group and 0.350 in the control group. The test statistics used was a two-sided *Z* test. The sample size was calculated using NCSS PASS (version 2008).

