### Primary study outcomes

All participants will be assessed for outcomes at 1, 3, 6, 9 and 12 months post discharge. The two arms will be compared with respect to:Proportion of participants adhering to medications prescribed (definition of adherence – use of prescribed medications on at least 5 days a week and measured by the locally validated Morisky Medication Adherence Scale [14]Proportion of participants achieving control of blood pressure (control is defined as BP <125/85), blood sugar (HbA1c <7 %) and blood cholesterol (LDL <100 mg/dl) [14]

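### The only analysis stated for the two binary primary endpoints is a screened, stepwise linear regression that neither names a primary between-arm estimate nor keeps the randomised arm in the final model

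*Protocol article*

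**What the plan says.** Under Primary study outcomes, the article states "The two arms will be compared with respect to" two items: "Proportion of participants adhering to medications prescribed", and "Proportion of participants achieving control of blood pressure (control is defined as BP <125/85), blood sugar (HbA1c <7" %) together with LDL cholesterol. Both are yes/no outcomes per participant. Sample size calculation assumes 0.50 against 0.35 and says of the method: "The test statistics used was a two-sided" Z test.

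The analysis of the primary endpoint is then given in two subsections.

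- **Univariate analysis:** "Multiple Linear Regression (MLR) will be applied at the univariate analysis level", and "Each variable will be regressed independently with the primary end-point". A variable counts as significant at this step if its p "value is less than or equal to 0.10". Significance is reported, with a crude coefficient and 95 % confidence interval.
- **Multivariable analysis:** "All variables that are considered to be significant at the univariate analysis level will need to run through a stepwise model building approach", done manually, to reach a parsimonious model. The threshold is p ≤ 0.05, the final model is again a linear regression, and its adjusted coefficients are reported.

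Neither subsection mentions the randomised arm. By contrast, Secondary end-points names a chi-square or Fisher test between groups for the binary secondary outcomes (readmission and mortality). The opening line of the Statistical analysis plan section sets analysis by initial allocation.

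**The concern.** This procedure is built to find predictors of an outcome. A randomised trial needs one treatment estimate per primary endpoint, fixed in advance and reported whatever its p value. Three things follow if the text is applied as written.

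1. Arm competes with every other variable for a place in the final model. If it fails a threshold, no adjusted treatment effect is reported; if it passes, the estimate has been filtered on its own p value.
2. The covariates are chosen from the data, by hand, and the confidence interval in the final model takes no account of that choice.
3. Nothing confines candidates to baseline variables. Knowledge scores are collected at every follow-up visit, and the videos are meant to change them. If such a score entered, it could absorb part of the effect the trial is meant to measure.

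The text also leaves open which result is the primary one: the crude coefficient for arm, the adjusted one, or neither.

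**Working it through.** **Inputs.** Control rate 0.35 and treatment rate 0.50; 150 per arm after 10 % inflation, so 150 × 0.9 = 135 evaluable per arm; two-sided test (all from Sample size calculation). Alpha is not given in that section and is taken as 0.05.

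**Step 1. Power of the test used for sizing.** With the pooled normal approximation,

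power = Φ{ [Δ√n − z·√(2p̄q̄)] / √(p₁q₁ + p₂q₂) }.

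Here p̄ = 0.425, √(2 × 0.425 × 0.575) = 0.6991 and √(0.25 + 0.2275) = 0.6910.

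- n = 150: (0.15 × 12.247 − 1.960 × 0.6991)/0.6910 = 0.676, power 75.0 %.
- n = 135: (0.15 × 11.619 − 1.960 × 0.6991)/0.6910 = 0.539, power 70.5 %.

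The stated power of at least 95 % is not reproduced; it would need 280 per arm before inflation. That is a separate matter, but it decides how the figures below must be read.

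**Step 2. Chance that arm fails the 0.10 screen.** Replacing 1.960 by 1.645 gives (1.743 − 1.150)/0.6910 = 0.858 at n = 135. Power is then 80.5 %, so arm fails in about 20 %. At n = 150 the value is 0.994, power 84.0 %, so arm fails in about 16 %.

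**Step 3. The whole rule against a plain test.** The stated rule was simulated as linear regression, a 0.10 screen, then backward elimination at 0.05 (1,500 trials per row). It used arm plus 10 covariates, 3 of them prognostic. The number and strength of covariates, and backward elimination as the form of the manual procedure, are assumptions. The plain two-sided Z test at 0.05, without covariates or selection, was enumerated exactly over the two binomial distributions.

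| Per arm | True difference | Rule: arm absent | Rule: mean when kept | Z test: not significant | Z test: mean when significant |
|---|---|---|---|---|---|
| 135 | 15 points | 28.9 % | 17.8 | 28.9 % | 17.9 |
| 135 | 10 points | 62.7 % | 15.7 | 60.2 % | 15.7 |
| 150 | 15 points | 24.1 % | 17.2 | 23.9 % | 17.3 |
| 150 | 10 points | 56.5 % | 15.0 | 56.9 % | 15.1 |

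A second simulation with 15 covariates, 5 of them weakly prognostic, gave 29 % and 17.7 points for the first row. The two procedures nearly coincide. The frequency with which arm is absent is one minus power, and the excess over the true difference comes from conditioning on p ≤ 0.05.

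**Step 4. What then differs.** After a Z test, the risk difference and its interval are reported in every trial. With arm kept in the model regardless of p, the mean estimate at 150 per arm and a true 15 points is 15.0 points. Under the stated rule, the adjusted effect is reported only in the filtered subset, so its mean there is 17.2 points.

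**Step 5. Linear model on a 0/1 outcome.** For arm alone, the coefficient is exactly the risk difference. Its squared standard error is (p₁q₁ + p₂q₂)/(n − 1), against (p₁q₁ + p₂q₂)/n for the usual unpooled form. At n = 135 the ratio of standard errors is √(135/134) = 1.004. In the enumeration at the 0.05 level, the linear-regression t test and the Z test gave the same decision for every pair of outcome counts, at both sample sizes.

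**The case against.** The strongest defence is that the randomised comparison is already there. If arm is one of the variables regressed singly, Univariate analysis yields its crude coefficient, interval and p value before any selection, and that is the risk difference with the same decision as the Z test. This stands. A reader might infer that the powered comparison is never run, or that a real effect could vanish from the report. The documents do not support that: what can be lost or distorted is the adjusted effect in the final model.

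A reader might also take 29 % and 17.7 points as damage done by stepwise selection. The comparison with the plain Z test shows that they are mainly a consequence of about 70 % power.

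Three further objections hold. The unequal variance of a binary outcome is immaterial for the arm contrast with equal arms. The 15 % change-in-coefficient rule is worded as a criterion for reporting confounding; that covariates are retained on it would be an inference. The article nowhere says that arm may be removed or that follow-up variables will be used. It is silent, and tracking a change in a coefficient ordinarily presupposes a main exposure, for which arm is the natural reading.

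One objection does not hold: that this is detail left to an unseen analysis plan. A covariate list could be left there. But the article itself fixes the model class, both thresholds, the selection method and what is reported from the final model, and its rule covers all variables without exemption. Analysis by initial allocation settles who is counted in which arm, but not whether arm stays in the model.

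**Conclusion.** The point holds in a limited form. For two binary primary endpoints, the article states a data-driven linear regression as the only analysis, names no between-arm estimate as primary, does not protect arm from selection and does not restrict candidates to baseline. As written, the adjusted treatment effect is missing when arm is non-significant and overstated on average when kept, with an interval that ignores the selection.

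The size is that of reporting an effect only when significant at this sample size. At the design difference, it is absent in about 24 to 29 % of trials and about 17 to 18 points instead of 15 when kept. Selection adds little to the non-significance a plain test would show; the harm lies in what goes unreported, in covariates picked from the data and in the possible entry of follow-up variables. That last part is not quantified.

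These conclusions rest on arm being treated like any other variable, on alpha 0.05, and on the assumed covariates and elimination rule. The 0.10 screen calculation needs no covariate assumption.

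**What to change.** For each primary endpoint, name the between-arm comparison of proportions as the primary analysis: two-sided Z (chi-square) test, with the risk difference and its 95 % confidence interval, reported whatever the p value. State the primary time point and reconcile the documents on it: the Abstract gives 12 months, while the hypothesis in Background and the Study question give 6 and 12 months.

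If a supporting adjusted analysis is wanted, use a binomial or logistic model that keeps arm regardless of its p value and contains only baseline covariates named in advance. Remove p-value screening and stepwise selection from the treatment comparison, and keep any search for predictors of adherence or risk factor control as a labelled exploratory analysis.

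The cost is wording only. No data collection, visit or sample size changes, and the amendment should be made before outcome data are seen by arm.

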In this study, we will assess the effect of video-based intervention on primary stroke survivors and their caregiver dyads on improving adherence to stroke preventive medications and control of three major risk factors at 6 and 12 months in a Pakistani population. Our rationale is to leverage the existing mobile phone infrastructure and use IT to deliver post-stroke education to dyads returning to the community and thereby improve post-stroke outcomes. We hypothesize that there would be a difference of at least 15 % in adherence to stroke preventive medications and control of three major risk factors at 6 and 12 months among stroke survivors who are given video-based education as compare to those who are given usual care.

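### The interaction check on the final primary model does not exempt the study arm, and no overall arm contrast is named as the primary result

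*Protocol article*

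**What the plan says.** The two sections headed Univariate analysis and Multivariable analysis are the only description of how the primary end-points are analysed. Each variable is first regressed alone on the primary end-point, and at that step "Crude beta-coefficient with 95 % confidence interval will also be reported". Variables with p ≤ 0.10 go forward and "will need to run through a stepwise model building approach (manual) to obtain a parsimonious model". The model type is linear: "Multiple linear regression (MLR) will be used to predict the final model". On reporting, "Adjusted beta-coefficients with their appropriate 95 % confidence interval will be reported for the final model". The next sentence adds that "The final model will be assessed for interaction between biologically plausible variables as well as for confounding after checking for interaction", with a 15 % change in beta as the confounding criterion. The only significance level given for this stage is in the sentence "A variable having a *p* value of less than or equal to 0.05 will be considered to be clinically significant as well as statistically significant".

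The trial's question is a single contrast. The hypothesis in the Background is that "there would be a difference of at least 15 % in adherence to stroke preventive medications" and in risk-factor control. The Primary study outcomes section says "The two arms will be compared with respect to" two proportions. The sample size rests on 0.50 against 0.35.

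**The concern.** The interaction check comes before the confounding check on the same model, so it reads as a model-building step and not as a separate subgroup analysis. The variables are not listed and the arm is not exempted. In an education trial, arm by disability or arm by risk factor would be natural candidates.

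Once a product of arm and covariate is in a linear model, the arm coefficient no longer answers the trial's question. It estimates the difference between arms among participants at the covariate's zero level, so its size, and possibly its sign, depends on which level was coded zero. This would be so even if the arm were always kept and every covariate were fixed in advance, which makes it a separate issue from stepwise selection. At stake is whether the coefficient taken as the main result is the overall difference the trial was sized for, or a less precise estimate for one subgroup.

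**Working it through.** **Inputs.** From the Sample size calculation: 150 per arm, 0.50 against 0.35, two-sided Z test, stated power at least 95 %. From Multivariable analysis: p ≤ 0.05. Assumptions, because the article gives no figure: alpha 0.05 for the sample size, interactions kept at p ≤ 0.05, independent binary covariates, and the number of interactions tested.

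**1. The plan's own power.** The mean proportion is 0.425.
- Null SE = √(2 × 0.425 × 0.575 / 150) = 0.0571.
- Alternative SE = √((0.35 × 0.65 + 0.50 × 0.50) / 150) = 0.0564.
- Power = Φ((0.15 − 1.96 × 0.0571) / 0.0564) = Φ(0.676) = 75 %.

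The stated 95 % is not reproduced; it would need 280 per arm. That is a separate matter. Here 75 % serves only as the benchmark for the overall contrast.

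**2. What the arm coefficient means.** With Y = b0 + b1·arm + b2·C + b3·arm·C and 0/1 coding, the arm difference is b1 when C = 0 and b1 + b3 when C = 1. The overall difference is b1 + b3 × (share with C = 1). Example with a 50/50 covariate: true effects of 0 and 30 points average 15. The arm coefficient estimates 0 with one coding and 30 with the other. In 4,000 simulated trials, its mean among models that kept the term was −0.02 with the first coding and 0.32 with the reverse, while the overall estimate stayed at about 0.15.

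**3. Precision when a term is kept.** The coefficient rests on the reference stratum.
- Half the participants in the reference category (75 per arm): SE ratio 1/√0.5 = 1.41. Power = Φ((0.15 − 1.96 × 0.0807) / 0.0798) = Φ(−0.103) = 46 %.
- 30 % in the reference category (45 per arm): SE ratio 1/√0.3 = 1.83, power 30 %.

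These are conditional on a term being in the model, and they ignore the selection that put it there.

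**4. How often a spurious term would be kept.** If k independent arm interactions are tested and none is real, the chance that at least one reaches 0.05 is 1 − 0.95^k.

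| k tested | chance |
|---|---|
| 1 | 5 % |
| 2 | 10 % |
| 3 | 14 % |
| 5 | 23 % |
| 10 | 40 % |

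The plan, however, checks interaction in the final model, so k is the number of covariates that survive selection. Simulating that sequence (univariate p ≤ 0.10, then multivariable p ≤ 0.05, arm kept in, 50/50 covariates, 3,000 trials per setting) gives:

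| Candidates | Truth | Mean surviving | Spurious arm interaction kept |
|---|---|---|---|
| 5 | none prognostic | about 0.25 | about 1 % |
| 10 | none prognostic | about 0.5 | about 3 % |
| 5 | three prognostic, 15 points each | about 2.4 | about 12 % |
| 10 | three prognostic, 15 points each | about 2.6 | about 12 % |

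**5. Upper range.** If all ten interactions were tested without prior selection, the rejection rate for the reported arm coefficient would rise from about 5 % to 17 % with no true effect. With a true 15-point effect, power would fall from 76 % to 66 %.

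**The case against.** The strongest reply is that the harm needs steps the article does not state. It does not say that the arm is among the variables checked, that a significant product term stays in the model, or that a reference-level coefficient would be presented as the trial's result. The handling of a detected interaction is commonly left to a statistical analysis plan, which is not shown. All of this stands, and it makes the point conditional. What remains is that the article does fix a data-driven interaction step on the primary model and names no contrast that the step cannot alter.

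A reader might infer that the plan offers no estimate of the overall effect. The text does not support that: if the arm is among the variables regressed singly, its crude coefficient is the full-sample difference in proportions. It appears only as a screening result, though, and is not ranked above the adjusted one.

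A reader might also infer that coefficients are reported after the interaction search. The reporting sentence in fact comes before the interaction sentence, and the order is left open.

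Finally, 23 % or 40 % might be taken as the expected frequency of a spurious term. Those figures need five or ten arm interactions to be tested, whereas the plan's selection would usually leave fewer covariates.

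**Conclusion.** The point holds in conditional form. The interaction step may involve the arm and no overall contrast is protected from it; if a term were kept, the arm coefficient would describe one covariate level. For a spurious term the likely frequency runs from about 1 to 3 % (no prognostic covariates) to about 12 to 14 % (two or three surviving), and reaches 23 % only if five are tested. The cost when it happens is a standard error about 1.4 times larger and power of about 46 % instead of 75 %, for an even covariate split, 150 evaluable per arm and two-sided 0.05. A real interaction would be kept more often, and the arm coefficient would then depend on coding. The documents do not show that the trial will report a subgroup effect as its answer. This is an inexpensive improvement worth making, not a fatal flaw.

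**What to change.** Add two sentences to Multivariable analysis. First: the treatment effect on each primary end-point is taken from a model that always contains the study arm and has no arm-by-covariate term, and this estimate with its 95 % interval is the primary result. Second: arm-by-covariate interactions are tested only in separate exploratory models for a short list named in advance, are reported as interaction estimates with 95 % intervals, and do not change the primary model.

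This needs no extra data or participants. The small downside is that a genuine effect modifier would appear only among the exploratory results.

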### Secondary end-points

To analyze the secondary outcome, caregivers’ mean score of knowledge regarding stroke risk factors, stroke rehabilitation and medications at each follow-up visit between the two groups will be calculated through Student’s *T* test if the outcome is symmetrically distributed or the Mann-Whitney *U* test if the outcome is not symmetrically distributed.

The proportion of participants with respect to readmission to hospital with any of the stroke-related complications between the two groups will be calculated either by Pearson’s chi-square test or Fischer’s exact test (if the expected cell count is less than 5).

The proportion of participants with respect to stroke-related mortality between the two groups will be calculated either by Pearson’s chi-square test or Fischer’s exact test (if the expected cell count is less than 5).

The change in mean score of National Institutes of Health Stroke Scale (NIHSS), Barthel Index and mRS from baseline at each follow-up visit between the two groups, will be calculated through Student’s *T* test if the outcome is symmetrically distributed or the Mann-Whitney *U* test if the outcome is not symmetrically distributed.

The change in mean scores for level of satisfaction with the intervention and acceptability of mHealth innovation at the third month follow-up visit post discharge between the two groups will be calculated through Student’s *T* test if the outcome is symmetrically distributed or the Mann-Whitney *U* test if the outcome is not symmetrically distributed.

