### Secondary study outcomes

Change in knowledge of caregivers concerning stroke risk factors, stroke rehabilitation and medications (a knowledge questionnaire will be administered at 1, 3, 6, 9 and 12 months post discharge and change in score will be ascertained)Readmission to hospital with any of the stroke-related complications – urinary tract infection, pneumonia, and deep venous thrombosis (this information will be elicited at the follow-up time, based on recall. All participants will be asked to bring documents related to any hospital admissions in the period following discharge)Stroke-related mortality will be assessed through a Verbal Autopsy Scale adopted from the WHO [15]Change in functional outcome (severity and disability after stroke) from baseline among stroke survivors will be assessed through validated tools (NIHSS, Barthel Index and mRS) [16]Level of satisfaction with the intervention and acceptability of mHealth innovation such as videos on selected topics among stroke survivors and caregiver dyads to improve clinical outcomes. This will be done on a self-designed tool which ascertains the constructive and unpleasant attributes of using this mHealth technology (please refer to Form C, Data Collection Form for Stroke Survivors– see Additional file 1). This self-designed tool will be administered by a research supervisor who will be unblinded to the randomization group. This tool has design attributes based on Rogers’ Diffusion of Innovation Theory for ease, adoption, repeatability, and adaptability [17].

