### Follow-up visits in the neurology clinic

Follow-up visits at 1, 3, 6, 9 and 12 months will be organized in the neurology outpatient clinic to assess outcome. In order to maximize our follow-up, participants will be sent short messaging service (SMS) reminders through our Stroke Helpline a day prior to the visit and transport will be arranged to facilitate the visit. If a stroke survivor along with their caregiver is not able to report for follow-up on the exact date, a grace period of ±14 days will be permitted to ensure capturing maximum follow-up. Those participant dyads that cannot appear for the follow-up in person will be contacted via phone or through establishing a follow-up visit appointment in synchrony with other clinical visits, physiotherapy sessions and laboratory investigations.

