While there is a relative lag in development of such centers, we plan to test and leverage our existing mobile infrastructure as a means of providing continuous care. Based on the current statistics by the Pakistan Telecommunication Authority, mobile phone users in Pakistan were recorded to number greater than 137 million and total cellular density had reached 77 % by 2014 [35]. In addition, mobile brands have introduced cheap Android Smart phones that are rapidly becoming mainstream and are expected to take over the larger market share, with the cheapest Smart phone starting from around US$6 [25]. Thus, we developed this interactive Android application.

mHealth applications have tremendous potential for chronic disease support. However, these software applications have not been tested in rigorous trial designs with clinically meaningful outcomes [36–38, 39].

The strength of this study is the use of a rigorous randomized controlled trial (RCT) design, measurement of intervention usage and fidelity, intervention delivery that is present both within the hospital and at follow-up, evaluation of clinically important outcomes and ITT analysis [40].

The limitations include the following: selection bias: this is a single center study chosen because of the fact that this site provides a standard of care that is algorithmic and replicable; thus, any results may be attributed to the intervention. In this study we may report its efficacy, but the performance in different sites may vary; contamination bias: in an educational intervention, care will have to be taken to avoid contamination of the non-intervention arm with the intervention. To ensure this, videos will be shown in a separate room, and not at the bedside. Given the fact that families do share information, contamination is possible; however, most stroke participants are on different schedules for visits, rehabilitation times, etc. and so we expect less contamination than in areas where a lot of time is spent together by families; attrition bias: many participants may drop out due to the longitudinal nature of the study. To counteract this, trained health care providers will try to follow the subjects closely through regular phone calls and build good rapport with them. A Stroke Helpline number will also be provided.

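### Caregiver knowledge is scored at five visits but compared one visit at a time, by a test chosen from the observed shape, so earlier scores do not inform later missing ones and no single effect estimate results

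*Protocol article*

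**What the plan says.** - **Schedule and definition.** Secondary study outcomes lists caregiver knowledge first and states that "a knowledge questionnaire will be administered at 1, 3, 6, 9 and 12 months post discharge and change in score will be ascertained".
- **Analysis.** Secondary end-points compares the caregivers' "mean score of knowledge regarding stroke risk factors, stroke rehabilitation and medications at each follow-up visit between the two groups will be calculated through" a two-sample t test "if the outcome is symmetrically distributed or the Mann-Whitney" test otherwise. The same either/or rule is used there for the functional scales.
- **How shape is judged.** Checking for normality and descriptive analysis says "Histograms will be graphed to check the distribution of all the continuous variables in the dataset". It gives no numerical criterion.
- **Loss to follow-up.** The sample size is set "after inflating 10 % to incorporate attrition and non-compliance". The Discussion adds that "many participants may drop out due to the longitudinal nature of the study". Follow-up visits in the neurology clinic provides a back-up: "Those participant dyads that cannot appear for the follow-up in person will be contacted via phone", or seen alongside another appointment.
- **Analysis principle.** "Analysis will be performed on the basis of initial treatment allocation", that is, intention to treat.

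The article states no repeated-measures model and no lead visit for knowledge.

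**The concern.** Five correlated scores per caregiver are treated as five unrelated two-sample problems. This has four consequences.

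1. A caregiver with scores at months 1 to 9 and none at month 12 adds nothing to the month-12 comparison, although the earlier scores predict the missing one. If low scorers leave more often, the arm with lower scores loses more of them. Its observed mean then rises more, and the observed difference shrinks towards zero.
2. The section names a mean, but Mann-Whitney compares ranks. It does not test a difference in means and does not estimate one. The quantity being compared therefore depends on what a histogram looks like after the data are in.
3. With five results and no lead visit, there is no one estimate to report for this end-point.
4. The outcome is a change in score in one section and the score itself in the other. These are different quantities, and the reference point for the change is not stated. The listed times start at month 1, after the enrolment and discharge videos. A change measured from month 1 would subtract any effect those two sessions had already produced.

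At stake are some precision, a possible modest bias towards no effect, and a clear answer on a secondary outcome.

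**Working it through.** **No plan figure to reproduce.** The protocol gives no power or effect size for knowledge; its sample size concerns the primary end-points. Everything below beyond the 150 per arm and the 10 % allowance is assumed: equal correlation between visits, a true month-12 difference of 0.35 SD, two-sided 0.05, and drop-out without return.

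**Step 1. Random drop-out, exact calculation.** Let loss rise linearly to 10 % at month 12. The fractions still observed at months 1, 3, 6, 9 and 12 are 0.992, 0.975, 0.950, 0.925 and 0.900.

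- Observed-only: n = 150 × 0.90 = 135 per arm; variance of the difference = 2/135 (SD = 1).
- Model: each arm's information matrix is Σ 150·w_k·A_k. Here w_k is the fraction last seen at visit k, and A_k is the inverse of the k × k correlation matrix padded with zeros. The effective n is the reciprocal of the month-12 diagonal element of the inverse.
- Power = Φ(0.35·√(n/2) − 1.96).

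| Loss | Correlation | Observed n per arm | Effective n, model | Variance ratio | Power, observed-only | Power, model |
|---|---|---|---|---|---|---|
| 10 % | 0.5 | 135 | 139.5 | 0.968 | 0.820 | 0.832 |
| 10 % | 0.7 | 135 | 142.8 | 0.946 | 0.820 | 0.841 |
| 20 % | 0.5 | 120 | 128.5 | 0.934 | 0.774 | 0.801 |
| 20 % | 0.7 | 120 | 134.9 | 0.890 | 0.774 | 0.820 |

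Example for the first row: 0.35·√67.5 = 2.876, and Φ(0.916) = 0.820; with the model, 0.35·√69.75 = 2.923, and Φ(0.963) = 0.832. At 10 % loss the exact variance reduction is 3 to 5 %. Simulations with slightly different drop-out patterns give about 2 to 6 %. The power gain is 1 to 2 points.

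**Step 2. Drop-out that depends on the last score, simulation.** 2,000 trials per setting; the log-odds of leaving rise by 0.8 for each SD lower on the last score. The observed month-12 difference is set against the likelihood estimate that uses all earlier scores.

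| Nominal loss | Observed-only estimate | Model estimate | Power gain |
|---|---|---|---|
| 10 % | about 0.33 to 0.34 | about 0.35 | about 3 to 4 points |
| 25 % | about 0.31 to 0.32 | about 0.35 | about 8 to 12 points |

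At the planned loss the bias is therefore about 0.01 to 0.02 SD, towards zero.

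**Step 3. Is the switch of test needed?** A score skewed against its ceiling was simulated: 0 to 20 points, 135 per arm, 3,000 null trials. The t test rejected in 4.97 %, so in this setting it keeps its error rate without a switch.

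**Step 4. If the choice is made separately at each visit.** Take 135 per arm, visit correlation 0.6, and a 5 % skewness test standing in for the unspecified check. Different visits would then get different tests in about 24 % of trials with normal scores, and in about 55 to 83 % with skewness of 0.2 to 0.45. This shows that mixed results are likely under that reading. It is not an error rate.

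**The case against.** The strongest replies concern what the text does not say.

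- **Attendees only.** A reader might infer that the comparison is limited to those who come to clinic. The documents do not say so. There is a 14-day window either side of each visit, with reminders, transport, phone contact and alternative appointments, and the analysis is by allocation. This reply stands. What remains is narrower: a two-sample test can use only scores that exist at that visit. Phone contact reduces gaps but cannot remove them; the Background itself cites 12 % first-year mortality in a hospital-based study. Analysis by allocation settles which arm a caregiver counts in, and does not supply a missing score.
- **Partial data thrown away.** A reader might also infer this. It is too strong, because every observed score enters its own visit's test. What is forgone is the use of earlier scores for later visits.
- **A different test at each visit.** This is one reading of the rule. The wording does not settle whether the choice is made once or five times. Harm from switching has not been shown as an inflated error rate.
- **Left to the analysis plan.** A method for missing data may lie in a plan that is not shown, so its absence is no fault here. The visit-by-visit tests and the choice by shape, however, are affirmatively stated.
- **Size.** The only attrition figure in the protocol is 10 %, and it includes non-compliance. The larger losses need about 25 % drop-out. This stands, and the conclusion is sized accordingly.

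**Conclusion.** The point holds in a limited form. The protocol commits to separate comparisons of the knowledge score at each visit, with the test chosen from the observed shape. This leaves earlier scores unused for later gaps, lets a rank test stand in for the mean that is named, yields no single effect estimate, and does not match the change-in-score definition.

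At the planned 10 % loss the statistical cost is small: about 2 to 6 % of variance if drop-out is random, or an estimate of about 0.33 to 0.34 instead of 0.35 and 3 to 4 power points if low scorers leave more often. It becomes material only if loss approaches 25 %. These figures rest on an assumed 0.35 SD effect, visit correlation 0.5 to 0.7 and the drop-out model above. The mismatch in definition and the missing single estimate rest on the text alone. This is a secondary outcome, and the trial's primary conclusion is not affected.

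**What to change.** - Replace the visit-by-visit tests with one pre-specified mixed model for repeated measures on the knowledge score: arm, visit, arm-by-visit interaction, unstructured covariance and robust standard errors. Add the baseline score as a covariate if one is collected. Use the model whatever the histogram shows.
- Name one lead visit in advance, for example month 12. Report its mean difference with a 95 % interval, and give the other visits from the same model.
- Keep Mann-Whitney only as a sensitivity check.
- Make Secondary study outcomes and Secondary end-points agree on score or change in score. If change is kept, state from which measurement.

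The cost is revised wording and slightly more programming, with no extra visits, data or participants. The model assumes that scores are missing at random given the observed ones, which should be stated.
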